### Sample size calculation

2.6

Based on previous results obtained in a MCT efficacy clinical trial (Ochoa et al., 2017) and accepting an alpha risk of 0.05 and a beta risk of less than 0.2 in a bilateral contrast, we would need 48 subjects to detect a difference equal to or greater than 1.7 units in the BCIS metacognitive variable, assuming a SD of 3.63. A loss to follow-up of 25% has been estimated.

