**Materials and methods:**

This is a unicentric randomized controlled trial of three parallel intervention groups: MCT, WA and combined intervention. The estimated sample will be 48 patients with a psychotic spectrum disorder diagnosis. The assessment will be performed at baseline and at 2-months’ follow-up. Instruments used in the assessment will include clinical, cognitive, metacognitive, social cognitive and psychosocial variables.

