
On one hand, we expect that WA intervention will improve physical health variables. On the other hand, we expect that MCT will improve variables related to symptoms and metacognition. Therefore, our main hypothesis is that the combined intervention will enhance the benefits of WA and MCT separately. The project will aim to evaluate the effects of each intervention, comparing the changes in the explored variables between the 3 intervention groups. Specifically, it is expected that the combined intervention will greatly facilitate an improvement in symptoms, cognition, metacognition, and psychosocial functioning. In addition, the transcript levels of the SP1 and SP4 biomarkers may change after the interventions, and it is anticipated that these changes will be even greater when the two interventions are combined.

The objectives of this project are:

To evaluate the efficacy of a combined intervention (WA and MCT) in people with schizophrenia or other psychotic disorders compared to each of the independent interventions on:Psychotic symptoms, cognition, metacognition, psychosocial functioning, and social stigmaMotor coordinationState of physical health: weight, height, BMI, abdominal circumference, blood pressure, heart rate, analysis that includes information on glucose, total cholesterol, HDL, and LDLStudy changes in the transcription levels of the SP1 and SP4 biomarkers depending on the intervention received (WA, MCT or combined intervention).Associate changes in SP1 and SP4 levels to improvements in symptoms, cognition, metacognition, social functioning, social stigma, motor coordination, and physical health status.

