### Study design

2.1

This is a unicentric randomized controlled trial with 3 parallel intervention groups. Participating services will recruit patients, and they will be randomized to each condition. Following baseline assessment, a random number table is used to assign each patient to one of the three conditions.

Conditions are (1) MCT, (2) WA, and (3) Combined Intervention (MCT and WA). The interventions include 8 weekly sessions, lasting approximately 2 months. We will perform post-treatment assessments right after the treatment ends. Upon completion of the last assessment, patients will be offered the opportunity to participate in any of the activities, regardless of the group assigned during the 2-month intervention. Details on the flowchart of the study can be seen in Supplementary Figure S1.

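### The stated power (beta below 0.2 for 1.7 BCIS units with 48 subjects) does not hold for comparisons between three randomised arms

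*Protocol article*

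**What the plan says.** Section 2.6 (Sample size calculation) bases the number on an earlier trial of metacognitive training. It works by "accepting an alpha risk of 0.05 and a beta risk of less than 0.2 in a bilateral contrast" and concludes that "we would need 48 subjects to detect a difference equal to or greater than 1.7 units in the BCIS metacognitive variable", with an SD of 3.63. A separate sentence gives an expected loss to follow-up of 25%. The section names no test, no pair of arms and no number per arm. It does not say whether 3.63 is the SD of the score or of the change.

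The abstract makes 48 the whole trial: "The estimated sample will be 48 patients with a psychotic spectrum disorder diagnosis". Section 2.1 (Study design) says: "This is a unicentric randomized controlled trial with 3 parallel intervention groups". The objectives in section 1 are to evaluate the combined intervention "in people with schizophrenia or other psychotic disorders compared to each of the independent interventions". Section 2.7 (Data analysis) plans repeated measures models that compare the three groups.

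**The concern.** A sample size justification should size the comparison that the trial makes. Here that comparison is between arms, and 48 patients in three arms leave about 16 randomised per arm, fewer after the expected loss. An SD of 3.63 against a difference of 1.7 is a standardised difference of 1.7/3.63 = 0.47. Arms of that size cannot usually detect such a difference.

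What is at stake is the meaning of a non-significant result. The article tells the reader that a true 1.7-unit difference would be missed less than one time in five. If power is near 20%, it would be missed about four times in five on any one contrast.

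**Working it through.** **Inputs.** From section 2.6: two-sided alpha 0.05 (z = 1.960), power 0.80 (z = 0.842), difference 1.7, SD 3.63, loss 25%. From the abstract: 48 in total. From section 2.1: three arms. The allocation ratio is not stated. I assume it is equal, which gives 48/3 = 16 randomised and 16 × 0.75 = 12 completers per arm.

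**Reproducing 48.** The one-sample or paired normal formula is n = [(1.960 + 0.842) × SD / difference]².
- (2.8016 × 3.63 / 1.7)² = 35.8, so 36 completers.
- 36 / 0.75 = 48.

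This uses every stated input and returns the stated figure exactly.

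**Between-arm requirement, same inputs.** The two-arm formula doubles the variance.
- 2 × 35.79 = 71.6, so 72 completers per arm.
- 72 / 0.75 = 96 randomised per arm.
- 3 × 96 = 288 in total, before any multiplicity adjustment.

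**What 48 gives between two arms**, if 3.63 is the SD of the quantity compared (noncentral t, two-sided 0.05):

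| | 12 per arm (25% loss) | 16 per arm (no loss) |
|---|---|---|
| Standard error, 3.63 × √(2/n) | 1.48 | 1.28 |
| Power for 1.7 units | about 20% | about 25% |
| Difference detectable with 80% power | about 4.3 | about 3.7 |

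The detectable difference at 12 per arm is 4.3/1.7 = 2.5 times the stated one. The 95% CI half-width at 12 per arm is 2.03 × 1.48 = 3.0 units, using the pooled error from three arms (33 df). An overall three-arm F test does no better. With a largest difference of 1.7 and 12 per arm, its power is 15% to 19%, depending on where the middle arm lies.

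**If 3.63 is the SD of the score and baseline is adjusted for**, the SD becomes 3.63 × √(1 − r²), where r is the baseline to follow-up correlation. The article gives no r, so I show a range:

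| r | Power, 12 per arm | Power, 16 per arm |
|---|---|---|
| 0.5 | 24% | 32% |
| 0.7 | 34% | 43% |
| 0.8 | 45% | 57% |
| 0.9 | 71% | 84% |

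At 12 per arm, 80% is reached only at r of about 0.92.

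**The case against.** The strongest reply is that section 2.6 names no test, so a paired calculation is an inference. That is right: the figure matches a paired calculation, and the documents do not establish that it is one. The loss stands in its own sentence, so 48 might be the number before loss. Two other routes reach 48 on that reading. One is a three-group analysis of variance with 0.468 entered as Cohen's f, which misuses a standardised difference. The other is a repeated measures interaction with f = 0.234 and an assumed correlation of 0.5. Both become 48/0.75 = 64 after loss, whereas the abstract gives 48 as the trial sample. Neither rescues the claim. Even with 48 completers, 16 per arm, power for 1.7 units is about 25%, or 32% with baseline adjustment at r = 0.5.

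It is also fair that 20% is conditional. The type of SD and the allocation ratio are not stated, and section 2.7 plans repeated measures models with covariates. A strong baseline correlation would raise power, to 84% at r = 0.9 with no loss at all. But the article reports no correlation and expects 25% loss, so this widens the range without supporting the stated power.

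A reader might go further in two ways that the documents do not support. One is to say that the combination must beat both single interventions, which would put power at about 9%. The objectives name both comparisons but set no such rule for success. The other is that the number invites within-arm before-after tests. Section 2.7 commits to comparing the three groups.

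**Conclusion.** The stated power is wrong for the trial's own question. With 48 patients in three arms, a 1.7-unit difference and an SD of 3.63, power between two arms is about 20% after the expected loss and about 25% without loss. This assumes equal allocation and that 3.63 is the SD of what is compared.

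The exact percentage moves with those assumptions. The conclusion that 80% is not delivered after 25% loss stands unless the correlation reaches about 0.92 with baseline adjustment. How the authors arrived at 48 remains an inference, and the conclusion does not depend on it. A fuller analysis plan could settle the type of SD and the model, but the number of patients would stay the same.

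**What to change.** Restate section 2.6 and leave the sample size as it is.
- Withdraw the claim of at least 80% power for a between-arm difference of 1.7 units.
- Name the test behind the number, say whether 3.63 is the SD of the score or of the change, and give the expected completers per arm.
- Give the between-arm figures for 48 randomised. On the assumptions above, with 12 completers per arm, these are power of about 20% for 1.7 units, a detectable difference of about 4.3 units and a 95% CI half-width of about 3.0 units. If the authors rely on baseline adjustment, they should state the correlation and its source.
- Report between-arm effects with 95% CIs, and state that a non-significant result is not evidence of no added benefit.

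The claim should not be replaced by 80% power for a before-after change in all completers pooled. The protocol poses no such question, the contrast has no control, and the exact paired t-test power at 36 is 78% (38 are needed for 80%).

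The cost is a rewritten paragraph and a less favourable stated power. The abstract gives only the number 48 and can stay.

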## Introduction

1

Schizophrenia and other psychotic spectrum disorders are severe mental disorders that affect around 1% of the population (Ochoa et al., 2008). Positive symptoms such as delusions and hallucinations usually respond to medication. Nevertheless, psychotic symptoms are sometimes resistant to antipsychotic medication, which is often not effective enough to achieve functional recovery (Morrison et al., 2018).

In this context, psychological treatment can help improve symptoms and functioning, even in the absence of pharmacological treatment (Morrison et al., 2014). Treatments such as Metacognitive Training (MCT) (Moritz and Woodward, 2007) have shown solid evidence for the improvement of psychotic symptoms. MCT is based on Cognitive-Behavioral Therapy and Psychoeducation, and it was developed to address cognitive biases and social cognition deficits in patients with psychosis. The focus of MCT is promoting reflectiveness on thought processes. It is widely used and effective in reducing positive symptoms, improving cognitive functioning, cognitive insight, immediate memory, and quality of life in schizophrenia (Moritz et al., 2014; Pankowski et al., 2016). Those improvements have already been established as possible in early stages of the disorder (Ochoa et al., 2017; Ruiz-Delgado et al., 2022). Moreover, previous studies have found that MCT can lead to immediate and sustained improvements in symptoms for individuals with psychosis (Moritz et al., 2014; Penney et al., 2022). In addition, evidence shows that MCT can be effective for both men and women with first-episode psychosis but target distinct aspects. Salas-Sender et al. (2020) found that after MCT, women with first-episode psychosis (FEP) experienced improvements in general symptoms, cognitive insight, and attributional style, while men showed a reduced presence of the jumping to conclusion bias.

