### Interventions

2.5

Participants who meet inclusion criteria will be randomized to one of 3 study conditions: (1) Metacognitive Training (MCT), (2) Water Aerobics (WA), and (3) Combined Intervention (MCT and WA).

Metacognitive Training (MCT): MCT consists of 8 group sessions of 1 h each and weekly frequency. Different metacognitive aspects related to the most common biases that occur in people with schizophrenia are worked on. The sessions are: attributional style, jumping to conclusions (2 sessions), changing beliefs, theory of mind and emotional recognition (2 sessions), memory errors and depression and mood. The groups are structured, include visual material, are entertaining and very participative and include discussions on how misinterpreting some situations can lead to exaggerated responses. Supplementary Table S2 shows each of the sessions of the MCT intervention.

Water Aerobics (WA): each weekly session will be 45–60 min in duration. Each activity (WA and MCT session) will take place once a week. Therefore, participants assigned to the combined intervention condition will attend both activities each week.

Participants assigned to the MCT condition will be offered WA after the completion of the study. Participants assigned to the WA condition will be offered to participate in a MCT group after the completion of the study. Participants assigned to the combined intervention condition will be offered the chance to continue participating in WA after the completion of the study, if interested.

An intervention guide will be developed in which Water Aerobics will be promoted. This guide will be elaborated by professional experts in physical activity science, physiotherapy, medicine, and sports psychology.

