One limitation of the study is the absence of reevaluation of the measures long term. Due to limited resources, the study only offers measures post-intervention, that mark the effectiveness of the combined training. Nevertheless, we expect that the benefits would persist in the long-term considering previous MCT studies (Moritz et al., 2014). In the same way, patients in this study are selected from different mental health services, in different stages of the disorder, with different severity impact. This could impact the clinical response, due to heterogeneity. Nevertheless, this heterogeneity could contribute positively, allowing the implementation of the interventions in several settings and stages. Another limitation could be that we have not considered tobacco dependence as an exclusion criteria, due to its possible effect on cognition and symptoms. We have not excluded tobacco dependence because of the high prevalence of patients with schizophrenia that consume it. Including this as an exclusion criteria would severely limit the possibility of recruitment, and it would reduce ecological validity. However, it would be interesting if further studies consider this variable, due to its possible effect in cognitive function (Núñez et al., 2015; Hickling et al., 2018; Ding and Hu, 2021).

Further studies should consider the profile of response to each of these two interventions, or its combination, in order to design a more personalized approach in their treatment, based on stages of the illness and the patients’ needs.

In summary, these results could be of great importance for the understanding, prevention and treatment of schizophrenia and other psychotic disorders.

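### The stated power for a 1.7-unit BCIS difference does not hold for combined versus MCT, a contrast for which the documents give no expected difference

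*Protocol article*

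**What the plan says.** Section 2.6 (Sample size calculation) takes its planning values from one source: "Based on previous results obtained in a MCT efficacy clinical trial". Under the error rates given there, "accepting an alpha risk of 0.05 and a beta risk of less than 0.2 in a bilateral contrast", it concludes that 48 subjects are enough to "detect a difference equal to or greater than 1.7 units in the BCIS metacognitive variable, assuming a SD of 3.63". It adds an expected 25% loss to follow-up. It does not say which comparison the 1.7 units refer to.

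The first objective in the Introduction sets the combination against each of the two single interventions, on outcomes that include metacognition. There are therefore two target contrasts: combined versus MCT and combined versus WA. On content, section 2.5 (Interventions) says that "participants assigned to the combined intervention condition will attend both activities each week".

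On expected effects, the Introduction says "we expect that WA intervention will improve physical health variables" and "we expect that MCT will improve variables related to symptoms and metacognition". It also puts forward a mechanism by which WA could act on prefrontal function, and expects the two together to give a larger gain in metacognition than either alone.

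**The concern.** Combined and MCT participants get the same MCT programme and differ only in whether they also get WA. On BCIS, this contrast asks what WA contributes on top of MCT, directly or by interaction. A trial of MCT efficacy informs a different quantity, namely what MCT does to BCIS. No section gives an expected value for combined minus MCT.

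Section 2.6 nevertheless attaches a power statement to the trial as a whole. A reader who sees beta below 0.2 next to an objective about the combination will take that objective to be adequately powered on BCIS. If combined versus MCT then turns out non-significant, it could be read as sound evidence that WA adds nothing, when the trial could say little either way.

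**Working it through.** **Inputs.** From section 2.6: difference 1.7, SD 3.63, two-sided alpha 0.05, power at least 0.80, total 48, loss 25%. From section 2.1: three arms. Assumed: equal allocation, as no ratio is stated. This gives 48/3 = 16 per arm and 16 × 0.75 = 12 completers per arm.

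**1. Reproducing 48.** The normal-approximation formula for a single group (or paired change) is n = [SD × (z0.975 + z0.80) / difference]² = (3.63 × 2.802 / 1.7)² = 35.8, rounded up to 36. Allowing for loss, 36/0.75 = 48 exactly. The stated number thus matches a pre-post calculation in one group.

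**2. The same inputs between two arms.** n per arm = 2 × (3.63 × 2.802 / 1.7)² = 71.6, rounded up to 72. Three arms need 3 × 72 = 216 completers, or 216/0.75 = 288 randomised. The 48 therefore does not give beta below 0.2 for a 1.7-unit difference between any two arms.

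**3. Precision of combined minus MCT.** With 12 completers per arm, the standard error is 3.63 × √(2/12) = 1.482. The 95% half-width is t(0.975, 22) × 1.482 = 2.074 × 1.482 = 3.07 units.

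**4. Power of combined versus MCT.** The true difference is not given, so a range is shown (two-sample t-test, two-sided 0.05).

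| Assumed true difference | 12 per arm | 16 per arm |
|---|---|---|
| 0.85 (half of 1.7) | 9% | 10% |
| 1.7 | 20% | 25% |

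The difference detectable with 80% power is 2.802 × 3.63 × √(2/n), which is 4.15 units at n = 12 and 3.60 at n = 16. Even twice the planning value (2 × 1.7 = 3.4) falls short of both.

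**5. Combined versus WA.** The arm sizes and SD are the same, so the half-width and the power for a given difference are the same.

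**6. Could baseline adjustment rescue it?** If 3.63 is the SD of scores, adjustment multiplies the variance by (1 − r²), where r is the baseline to follow-up correlation. To bring 4.15 down to 1.7 requires 1 − r² = (1.7/4.15)² = 0.168, so r = √0.832 = 0.91. At 16 per arm, 1 − r² = (1.7/3.60)² = 0.223, so r = 0.88. If 3.63 is already the SD of change, the factor is (1 + r)/2, which is at least 0.5 for non-negative r. The detectable difference at 12 per arm is then at least 4.15 × √0.5 = 2.93. The documents give no correlation.

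**The case against.** The best defence is that section 2.6 names no contrast and never claims power for combined versus MCT in so many words. The 1.7 could also be meant as a smallest difference of interest, which would apply to any comparison. But the text ties the planning values to results of an MCT trial and does not call 1.7 a relevance threshold. Even on that reading, power for 1.7 between arms is about 20 to 25%, so the beta claim still fails.

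A second defence is that the investigators hypothesise synergy. That stands as far as it goes. A reader might infer that the MCT effect simply cancels and that combined minus MCT can reach 1.7 only if WA alone moves metacognition as much as MCT does. This holds only under additivity, and the Introduction expects more than additive benefit. The difference could be small or large; the documents do not estimate it. Synergy makes this contrast central to the main hypothesis but supplies no planning value for it.

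Third, the half-width of about 3.1 units is a consequence of small arms and applies to every pair. That is correct, and it is why combined versus WA must not be presented as the contrast that was properly sized. A reader might infer that 1.7 belongs to combined versus WA alone. The text does not say so, and the 48 is reproduced only by a single-group calculation.

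Finally, a reader might infer that 1.7 and 3.63 come from an early-stage sample and do not carry over. The Introduction does cite the source trial, with another, for the statement "Those improvements have already been established as possible in early stages of the disorder", and section 3 describes the present patients as being "in different stages of the disorder, with different severity impact". But section 2.6 does not describe the source trial's sample, section 3 makes no comparison with it, and the heterogeneity is already disclosed as a limitation. That inference is too weak to rely on.

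**Conclusion.** The point holds as a mismatch between a stated property and the design. Section 2.6 claims beta below 0.2 for 1.7 BCIS units with 48 subjects. For combined versus MCT, one of the two contrasts in the main objective, the documents offer no expected difference, and power would be about 20% with 12 completers per arm (25% with 16) even if the difference were 1.7. The expected 95% half-width is about 3.1 units.

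This rests on equal allocation, on 25% loss, and on 3.63 being usable for a between-arm comparison without adjustment. The protocol does not say whether it is an SD of scores or of change. Baseline adjustment may narrow the interval, but would need a very high correlation to restore the stated power.

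A reader might also infer that WA's added value ought to be judged on physical-health outcomes instead. The documents do not support that as a correction: the investigators hypothesise a gain in metacognition too, and physical health is already an objective compared across the three groups.

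**What to change.** In section 2.6:

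- State that the 1.7-unit figure comes from an MCT efficacy trial and is not an estimate of combined minus MCT.
- Withdraw the beta-below-0.2 statement for the between-arm contrasts, or restate it with the precision to be expected: a 95% half-width of about 3 units on BCIS before any gain from baseline adjustment. Apply this to combined versus WA as well as combined versus MCT.
- State that combined versus MCT on BCIS will be reported as an estimate with its 95% confidence interval, and that a non-significant result will not be read as WA adding no benefit.

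The cost is a rewording of section 2.6 and one sentence on interpretation, with no extra patients or measurements. The downside is that the stated justification for 48 becomes less favourable.

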## Abstract

**Background:**

Metacognitive Training (MCT) is widely used and effective in reducing positive symptoms in psychosis. Physical exercise, such as Water Aerobics (WA), improves general health, quality of life and symptoms as a low impact activity that allows social interactions. Preliminary results suggest a relationship between dopamine and psychotic symptoms, through SP transcription factors, SP1 and SP4 biomarkers. The aims of the project are to evaluate the efficacy of a combined intervention (WA and MCT) for psychosis to improve psychotic symptoms, physical health, and transcription levels of SP biomarkers.

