### Data analysis

2.7

Repeated measures models will be performed comparing the results of the three groups according to the study variables, clinical, cognitive, metacognitive, and social functioning, social stigma, motor coordination, physical health status, as well as biomarker variables. We will include as covariates those variables that show significant mean differences between groups in the baseline assessment. Additionally, we will control by sex, age, antipsychotic dose (chlorpromazine levels) and symptom severity, since these are variables that have been associated with our main outcomes.

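### No primary outcome is named: the trial is sized on BCIS, but BCIS has no special status among about 20 unranked outcomes

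*Protocol article*

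**What the plan says.** Four places in the protocol article bear on which outcome the trial is designed to answer.

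- **Abstract, Background.** The combined intervention is to be evaluated for its efficacy "to improve psychotic symptoms, physical health, and transcription levels of SP biomarkers". Metacognition is not in this list.
- **Introduction, objectives.** The list is wider: symptoms, cognitive and metacognitive function, psychosocial functioning, stigma, motor coordination, ten physical-health items, and SP1 and SP4. The combination is to be compared with each single intervention. No item is placed above another.
- **Section 2.6.** The only sample size calculation is set up to detect a difference equal to or "greater than 1.7 units in the BCIS metacognitive variable, assuming a SD of 3.63", "accepting an alpha risk of 0.05 and a beta risk of less than 0.2 in a bilateral contrast". It does not say which BCIS score is meant.
- **Section 2.7.** Repeated measures models compare the three groups on all of these domains. The fixed covariates are justified on the ground that "these are variables that have been associated with our main outcomes". The main outcomes are plural and are not identified there or elsewhere in the article.

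**The concern.** The primary outcome and its link to the sample size are things a protocol has to fix itself, even when testing mechanics are left to an analysis plan. Here the abstract, the objectives and the sample size paragraph each imply a different outcome or set of outcomes, and the analysis section does not choose between them. BCIS, the only outcome with a power statement, receives no priority in the analysis.

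What is at stake is how the result is read. Section 3 anticipates that confirmed hypotheses would argue for pairing psychological treatment with exercise. With no outcome ranked, a favourable finding on symptoms, weight, cholesterol or an SP transcript could each be offered as that support. The power claim would then not apply to the outcome being reported, and the reader could not tell which result a 5% error rate was meant to protect.

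**Working it through.** **1. The plan's own figure.** Inputs from section 2.6: difference 1.7, SD 3.63, two-sided alpha 0.05, power 80%, 25% loss.

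One-group (pre-post) normal formula: n = ((1.960 + 0.842) × 3.63/1.7)² = 35.8, so 36. Allowing for loss: 36/0.75 = 48.

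This matches the stated 48, with 3.63 read as the SD of change. The two-group formula does not: n = 2 × 35.8 = 71.6, so 72 evaluable per arm. That is 216 for three arms, or 216/0.75 = 288 after loss.

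**2. Power for BCIS on the comparison in the objectives.** The allocation ratio is not stated. Assuming 1:1:1, 48/3 = 16 per arm, and 16 × 0.75 = 12 after loss. Power ≈ Φ(1.7/(3.63 × √(2/m)) − 1.96).

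- m = 16: 1.7/1.283 = 1.325; Φ(−0.635) = 26%.
- m = 12: 1.7/1.482 = 1.147; Φ(−0.813) = 21%.

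For 80% power the SD would have to fall to about 1.7 at 16 per arm, or about 1.5 at 12.

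**3. Number of outcomes** (objectives and section 2.3), counting one measure per clinical or psychosocial domain:

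- clinical and psychosocial domains: 5
- motor coordination: 1
- body and vital-sign measures: 6
- metabolic measures: 4
- SP1 and SP4, each as protein and as mRNA: 4

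The total is 20, or 18 if each SP factor counts once. Several instruments per domain would raise it; the instrument list is in a supplement that is not shown.

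**4. Chance of at least one false positive.** This assumes no true effects and a 5% test of each outcome. The 5% is carried over from the sizing paragraph.

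Independent outcomes, one test each: 1 − 0.95²⁰ = 64% (18 outcomes: 60%; 22 outcomes: 68%).

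The outcomes are not independent, so three-group data were simulated with 20 outcomes at 12 and 16 per arm. The documents give no correlations; those below are assumed.

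| Assumed correlation | One three-group test per outcome | Two contrasts per outcome (combined vs each single arm) |
|---|---|---|
| None | 64% | 85% |
| Blocks: 0.3 within, 0.1 between | 59% | 80% |
| Blocks: 0.5 within, 0.1 between | 54–55% | 75% |
| Blocks: 0.7 within, 0.1 between | 45–46% | 66% |
| 0.3 throughout | 55% | 75–77% |
| 0.5 throughout | 43–44% | 63% |

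The range is therefore about 43–64% with one test per outcome and about 63–85% with two contrasts.

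**The case against.** A reader might infer three stronger claims, and the article does not support any of them.

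*BCIS lies outside the trial's aims.* It does not. The objectives list metacognition, the Introduction expects MCT to improve it, and the abstract's methods include metacognitive variables. The omission is confined to the abstract's statement of aims.

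*Everything is tested at 5% with no multiplicity control.* The value 0.05 appears only in section 2.6. Section 2.7 gives a model family and covariates, but no test level and no success rule. A multiplicity rule may stand in an analysis plan that is not shown, so its absence from a condensed article is not a fault.

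*A chance positive is more likely than not.* The 64% needs 20 independent tests with no true effects. BMI is computed from weight and height, total cholesterol moves with LDL, and adult height will not respond to a two-month intervention. With one test per outcome the figure can fall below 50%. It stays above 50% across the assumed correlations only with two contrasts per outcome. The objectives imply those contrasts, but section 2.7 does not specify pairwise tests.

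It is also fair to say that the choice of primary outcome, and of which outcomes become exploratory, belongs to the sponsor.

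These objections limit the wording but leave the core standing: the article names no primary outcome, leaves its main outcomes undefined, and gives the sized variable no priority.

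**Conclusion.** The point holds as an inconsistency over what the trial is designed to show. The sizing rests on BCIS, the abstract's aims leave out its domain, the objectives include it without rank, and the analysis treats all domains alike. A positive result on any of about 20 variables could be presented as efficacy, although the power statement covers only one.

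The size of the risk is conditional. It is about 43–64% or 63–85%, according to the number of contrasts per outcome, and it rests on an assumed 5% test level, assumed correlations and no true effects. The count of about 20 is probably a minimum.

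Naming BCIS as primary would not settle the matter alone. The stated 80% power reproduces only as a one-group contrast. On the same figures a between-arm contrast has about 21–26% power, assuming equal allocation and 3.63 as the SD of the quantity compared. A smaller residual SD after baseline adjustment would raise this, but the article gives none.

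**What to change.** - Name one primary outcome at 2 months that matches the sample size basis. If BCIS is kept, state which score.
- Test it by combined versus MCT and combined versus WA. State whether both contrasts must succeed or how alpha is shared between them, for example by Holm.
- Align the abstract's aims, the objectives and section 2.7 with that choice, and replace the undefined reference to main outcomes.
- Put a short list of key secondary outcomes under Holm or false-discovery control. Report the rest as supportive or exploratory estimates with confidence intervals. The sponsor decides which outcomes fall in which group.
- Restate the power in section 2.6 for the between-arm contrast, with the allocation ratio and the SD that applies to it.

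The cost is wording, with no new data or visits. The downside is that fewer outcomes can support a confirmatory claim. Restating the power may also show that 48 participants are too few for a confirmatory between-arm test on BCIS.
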